## Abstract

**Background:**

Systematic reviews have shown that exercise therapy and spinal manipulation are both more effective for low back pain (LBP) than no treatment at all. However, the effects are at best modest. To enhance the clinical outcomes, recommendations are to improve the patient selection process, and to identify relevant subgroups to guide clinical decision-making. One of the systems that has potentials to improve clinical decision-making is a treatment-based classification system that is intended to identify those patients who are most likely to respond to direction-specific exercises, manipulation, or stabilisation exercises.

**Methods/Design:**

The primary aim of this randomised controlled trial will be to assess the effectiveness of a classification-based system. A sample of 150 patients with subacute and chronic LBP who attend a private physical therapy clinic for treatment will be recruited. At baseline, all participants will undergo a standard evaluation by trained research physical therapists and will be classified into one of the following subgroups: direction-specific exercises, manipulation, or stabilisation. The patient will not be informed about the results of the examination. Patients will be randomly assigned to classification-based treatment or usual care according to the Dutch LBP guidelines, and will complete questionnaires at baseline, and 8, 26, and 52 weeks after the start of the treatment. The primary outcomes will be general perceived recovery, functional status, and pain intensity. Alongside this trial, an economic evaluation of cost-effectiveness and cost-utility will be conducted from a societal perspective.

**Discussion:**

The present study will contribute to our knowledge about the effectiveness and cost-effectiveness of classification-based treatment in patients with LBP.

**Trial registration:**

Trial registration number: NTR1176

## Background

Low back pain (LBP) is a common condition. It has a lifetime prevalence of over 70% in industrialised countries, and accounts for considerable healthcare and socioeconomic costs [1,2]. It is often not possible to make a specific diagnosis based on patho-anatomical causes, and 85-95% of the cases are diagnosed as "non specific" LBP [3]. The lack of a clear patho-anatomical basis for LBP has resulted in a large variation in LBP diagnoses, and a multitude of poorly studied interventions [4]. It has been assumed that randomised controlled trials (RCTs) could provide answers to questions such as 'which intervention is most effective for which patient', but after the publication of more than 1,000 RCTs focusing on LBP, there is still a lack of evidence regarding the most effective strategies for matching individual patients to specific interventions. The Cochrane Back Review Group acknowledged the limited role of RCTs in providing useful information on aspects of LBP management other than efficacy and effectiveness, and stated that additional etiological, diagnostic, and prognostic studies are needed to identify varieties of LBP, natural courses, or more homogeneous subgroups of patients with LBP [5]. The identification of homogenous subgroups according to evidence-based classification systems was determined as a priority for primary care research on LBP as early as 1996 [6].

Over the years, many attempts have been made to classify patients with LBP into more homogeneous subgroups, based on the specific interventions that they are likely to respond to. In 2007, Billis et al. identified 39 diagnostic and treatment-based classification systems [7]. Most of the classification systems were based on biomedical patient characteristics, and seldom on psychosocial or biopsychosocial features. The majority of the classification systems was based on a judgemental approach, relying on clinical experience and intuition, and a minority was based on a statistical approach and prospective study designs.

One of the few classification systems that has potentials to improve outcomes is a treatment-based classification approach, originally proposed by Delitto et al. [8]. This approach is based on the patient's history, clinical presentation, and a physical examination. It identifies subgroups of patients who are most likely to respond to the following interventions: (1) direction-specific exercises, (2) manipulation, (3) stabilisation, and (4) traction. Since the early nineties, several derivation and validation studies have focused on these four interventions and the entire classification system (Additional file 1) [9-20]. Two studies have investigated the validity of the entire classification system, but because the studies used different RCT designs, they answered different research questions. Fritz et al. [12] investigated the effectiveness of the overall treatment approach of the classification system (classification decision-making and treatment protocols), whereas Brennan et al. [18] focused on the effectiveness of the classification decision-making. In a RCT, Fritz et al. [12] compared treatment according to the classification system with treatment according to the clinical guidelines (low-stress aerobic exercises and advice to remain active) for 78 patients with acute, work-related LBP. They found statistically significant better results for the outcomes of disability and return to work in patients who were receiving classification-based treatment at the four-week follow-up, but not at the one-year follow-up. Their research addressed the efficacy of the overall treatment approach of the classification system. However, the results may have been influenced by the treatment protocols that were used, and not the classification decision-making process. Brennan et al. [18] classified 123 patients with a duration of LBP of less than 90 days according to the classification system. All patients were randomised to receive direction-specific exercises, manipulation or stabilisation, regardless their classification. Outcomes were compared between patients who had received 'matched treatment' (according to the classification) and 'unmatched' (non-classification) treatment. The authors found a statistically significant reduction in disability, favouring the matched treatment group after 4 and 52 weeks.

The reliability of the classification system has been assessed in four studies. In a study of 43 patients with acute LBP, Fritz et al. [21] investigated the inter-rater reliability of the classification of patients into one of the subgroups by 7 physical therapists (PTs) who were familiar with the system. They achieved a kappa value of 0.49. Kiesel et al. [22] achieved a slightly higher kappa value (0.65) with 8 PTs who were familiar with the classification system and 30 patients with LBP. Heiss et al. [23], in a study in which 45 acute LBP patients were classified by four PTs who were unfamiliar with the classification system, found a low kappa value (0.15). Finally, Fritz et al. [24] investigated the inter-rater reliability of the system in a vignette study with 30 PTs and 123 LBP patients, and reported a kappa value of 0.60. These findings therefore provide preliminary evidence that PTs who are familiar with the classification system can obtain an acceptable level of intra-rater reliability.

It is essential for a treatment-based classification approach to be dynamic, and to incorporate new evidence. Since the original proposal, made by Delitto and colleagues, the criteria for allocating a patient to a specific intervention, and also the intervention procedures, have been revised and updated. However, although this continued evolution of a classification system is necessary in order to incorporate emerging evidence, it does reduce the comparability of studies using different versions of the treatment-based classification approach, and should motivate continued research on the approach.

In summary, the classification system proposed by Delitto and colleagues [8] has evolved considerably, and some promising results have been reported. However, the evidence for its clinical usefulness is still limited. Therefore, the aim of the present study is to evaluate the cost-effectiveness of classification-based treatment, compared to usual care according to national clinical guidelines, in patients with subacute and chronic LBP in primary care in the Netherlands. The present study will focus on a revised version of the Delitto et al. treatment-based classification system [8], based on updated evidence outlined in previous RCTs [25], but is consistent with the concept that sub-groups of patients can be identified, and that the primary subgroups are patients who are likely to respond to direction-specific exercises, stabilisation or manipulation. The aim of this paper is to describe the rationale and design of the study.

## Methods/Design

### Design

A randomised controlled trial will be conducted, together with a full economic evaluation. Figure 1 provides an overview of the study design.

**Figure 1 F1:**
[figure not shown]
**Design of the study**.

### Setting

Up to 300 private physical therapy clinics, with more than 1,000 PTs in the city of Amsterdam and the surrounding (rural) area (< 50-kilometre radius), will be invited to participate.

### Ethical approval

In February 2008, the Medical Ethics Committee of the VU University Medical Centre in Amsterdam approved the study protocol (registration number: 2008\5).

### Study population

The study population will consist of patients who seek care in a participating private physical therapy clinic. The inclusion criteria will be: LBP as primary complaint, with or without associated leg pain, age between 18 and 65 years, current episode >6 weeks, able to speak and understand Dutch, and willing to give written informed consent. The exclusion criteria will be: known or suspected specific LBP (e.g. cauda equina compression, fractures), severe radiculopathy, spondylolisthesis (grade 2 or more), serious co-morbidity, serious psychopathology, lumbar spinal surgery in the previous year, more than one low back operation, more than one year of absence from work due to LBP, pregnancy or given birth in the past three months, inability to attend 6 or more regular physical therapy appointments, moderate complaints about one or more items of the Urogenital Distress Inventory (UDI 6, short form) or inability to demonstrate any LBP symptoms during mechanical examination.

### Recruitment of patients

PTs will inform all eligible LBP patients who attend their clinic about the study. Subsequently, the principal investigator (AA) will phone potentially eligible patients to explain the trial procedures in detail and to check the selection criteria. If a patient fulfils the initial requirements for eligibility, an appointment will be made at the private physical therapy clinic that the patient attended, where the patient will be asked to sign an informed consent form and to complete baseline questionnaires. The patient will then undergo a physical examination.

The PTs will also be asked to collect basic data from eligible patients who are not willing to participate, and to record their reasons for declining.

### Research physical therapists

All patients will be examined by one of four research PTs, all of whom have followed a post-graduate course in manipulation and mobilisation techniques, and are certified manual therapists (MTs) in the Netherlands. Two research PTs have a Mechanical Diagnosis and Therapy certificate (MDT or McKenzie method). The two research PTs with no MDT certificate attended a one-day MDT training session supervised by a senior educator of the MDT Institute ([name]) to familiarise them with the MDT system. Prior to the study, the research PTs held meetings to standardise the examination protocol, to train in examination techniques and to examine patients together. The research PTs will examine and classify the patients, but will not be involved in providing the intervention.

### Classification system

The classification system that will be used in this study is a revised version of the system used by Brennan et al. [18]. The classification system is a decision-making procedure that is used to allocate patients to one of the following treatment categories: direction-specific exercises, manipulation, or stabilisation (Figure 2).

**Figure 2 F2:**
[figure not shown]
**Modified treatment-based classification system for patients with LBP (>6 weeks) as used in this RCT**.

### Baseline examination

The examination procedure will start with a standardised history-taking, which will include questions on the frequency of episodes, current duration, intensity, and location of the symptoms. Subsequently, a standardised comprehensive physical assessment will be made, together with a neurological examination if indicated. The examination starts with the determination of a directional preference, based on the definition proposed in the MDT classification method (step 1 in Figure 2) [26]. This involves the monitoring of symptomatic and mechanical responses during repetitive end-range lumbar test movements (flexion, extension, side-gliding, or rotation) and/or prolonged positioning. A directional preference is established if certain postures or repeated end-range movements in one direction (e.g. flexion) cause the symptoms to improve or centralise (pain moves from a distal to a proximal area), and in the opposite direction (e.g. extension) cause the symptoms to worsen or peripheralise (pain moves from a proximal to a distal area). Priority is given to peripheral pain locations and their response, regardless of the response of the central pain intensity. The improved or centralised symptoms must be retained in a neutral standing position. A directional preference is not established if the symptoms and the pain immediately reappear. For the sake of clarity, patients with a directional preference do not necessarily have centralisation of the symptoms. After this assessment, several other physical tests, such as the prone instability test, thigh thrust test, and the active straight leg raise test will be performed (step 2 in Figure 2). The operational definitions of these tests are summarised in the Appendix (Additional file 2). The classification decision-making has a hierarchical structure, however, all patients will undergo the entire examination procedure. In cases of uncertainty about the primary classification, extra criteria, such as three or more prior LBP episodes in the medical history and a visible lateral shift during the examination, will be used to determine the patient's subgroup (step 3 in Figure 2). Directly after this examination the research PT will determine the patient's classification and the level of firmness of the conclusion: level 1. there is an obvious primary classification; level 2. two of the three classifications are plausible; and level 3. none or all of the three classifications are plausible. The patient will not be informed about the results of the examination. Reasons for exclusion, such as inability to demonstrate any LBP symptoms during the examination, will be registered. It is the intention that the principal investigator (AA) will examine all patients. To identify patients reliably, one of the three other research PTs, depending on availability, will attend the examination procedure. When two research PTs examine a patient, the primary classification will be reached by consensus.

### Treatment allocation

To conceal the treatment allocation, an independent researcher who is not involved in the selection of the patients will randomise each patient to one of the two treatment groups. Randomisation lists will be generated by computer before the study starts, pre-stratified for the duration of the complaints (6-12 weeks or >12 weeks) and disability (Oswestry Disability Index [ODI] <25% or ≥25%) to prevent unequal distribution. To prevent unequal treatment-group sizes, the patients will be randomised according to a stratified block randomisation method, in blocks of four. No treatment will be given prior to randomisation.

Directly after the randomisation procedure, the PT who will provide treatment will be informed about the group allocation. Patients will be scheduled for their first treatment session as soon as possible in the private practice they attended.

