#### III. Stabilisation

First, the patients will be taught to activate their local stability system to control neutral joint position in a supine position [29]. This (slight) co-activation of the lumbar multifidus with the transversus abdominus ('drawing in' the stomach) must be accompanied by minimal trunk movements and relaxation of global muscles such as the upper abdominal muscles. The patients will then be instructed to perform these abdominal bracing exercises ('drawing in' the stomach with normal breathing) during strengthening exercises in standing, quadruped, and side-support positions. Apart from these standardised exercises, activity of the local and global muscle systems will be trained in positions and movements that aggravate the patient's pain, in order to restore functional capacity and to improve dynamic control. The patients will also receive an instruction booklet, and will be instructed to perform the exercises once a day and to keep self-monitoring exercise diaries.

For all classification-based interventions, the treatment frequency, amount and type of exercises, and the duration and progression of the programme will be recorded, and directed by the judgment of the PT. The treatment frequency will only be restricted for spinal manipulation (maximum of 6 sessions). The patients will be treated according to their primary classification for a minimum of 4 weeks, during which the PT will be allowed to change the treatment strategy, if (1) the functionality of the patient improves significantly (a reduction of >30% on the ODI, compared to the score at baseline) or (2) the symptoms are severely aggravated. After the first 4 weeks, the PT will be allowed to provide follow-up interventions. At the end of each patient's treatment period, the PT will note the degree of satisfaction with the classification-based treatment, measured on a 5-point Likert scale ranging from very satisfied to very dissatisfied.

In both treatment groups, the patients are requested not to receive any co-interventions apart from the physical therapy (such as complementary and/or alternative medicine [CAM]) during the intervention period. All patients will be asked to stay active, and to engage in general exercise activities (e.g. a sports club). The principal investigator will regularly monitor the PTs for compliance with the treatment protocols, by means of visits, phone calls and e-mail contact.

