### Blinding

The PTs will be asked not to disclose the treatment allocation to the patients, and the success of the blinding will be evaluated at the 8-week follow-up. The research assistants and the participating statistician will be blinded for the patient's group assignment. The research PTs and the treating PTs cannot be blinded for the treatment allocation, but they will not be involved in the outcome date-collection.

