### Sample size

Power calculations, based on the studies carried out by Brennan et al. [18] and Fritz et al. [12], were performed for the 3 main outcomes (for all: power 0.9; alpha 0.05). To detect a clinically relevant mean difference between the classification group and the usual care group of 9 points on the ODI (standard deviation [SD] 16), 55 patients are needed per group. To detect a clinically relevant mean difference of 2 points (SD 2) for pain (11-point numerical rating scale), 2 groups of 21 patients are needed. To detect a 20% difference in the dichotomised global perceived recovery (recovered vs. not recovered), 68 patients are needed per group. Anticipating a potential drop-out of 10%, 75 participants per treatment group (total n = 150) will be recruited.

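### Fixed blocks of four, with an unblinded principal investigator examining patients while exclusion is still open, could let up to a third of allocations be worked out in advance

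*Protocol article*

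**What the plan says.** Under Treatment allocation, computer lists are prepared before the study starts and "an independent researcher who is not involved in the selection of the patients will randomise each patient". There are four strata: symptom duration (6-12 weeks or longer) by ODI (below 25% or not). Within them "the patients will be randomised according to a stratified block randomisation method, in blocks of four". No variation in block size is mentioned. Under Sample size, "75 participants per treatment group (total n = 150) will be recruited", so allocation is 1:1.

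The principal investigator has several roles:

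- Under Recruitment of patients, this person "will phone potentially eligible patients to explain the trial procedures in detail and to check the selection criteria". The patient then attends, completes the baseline questionnaires and is examined, in that order.
- Under Baseline examination, this person intends to examine all patients. Exclusion is still possible at that point: "Reasons for exclusion, such as inability to demonstrate any LBP symptoms during the examination, will be registered". The classification and its level of firmness are also set then.
- In the paragraph on both treatment groups that closes the description of the interventions, "The principal investigator will regularly monitor the PTs for compliance with the treatment protocols". Under Physical therapists in the participating clinics, each therapist delivers only one arm.
- Under Blinding, "The research PTs and the treating PTs cannot be blinded for the treatment allocation". The principal investigator is one of the research therapists.

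**The concern.** Keeping the list with an independent person hides it from the examiner. It does not stop the examiner from deducing the next entry when the block size is fixed and known and earlier allocations are visible. Once two patients in a block of four have gone to one arm, whatever remains of that block must go to the other.

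The article gives a route to that knowledge. Since each therapist works in one arm only, knowing which therapist treats a patient reveals the arm, and the principal investigator is in regular contact with those therapists. The same person then judges whether a patient's symptoms can be reproduced on examination, which decides whether the patient stays in, and takes part in the classification.

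Concealment carries much weight in this trial. All three primary outcomes are self-reported, the treating therapists know the arm, and patient blinding depends on therapists being asked not to disclose it. Foreknowledge at a judgement-based exclusion step could make the arms differ at entry in ways that adjustment for measured baseline variables would not fully remove.

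**Working it through.** The article states no predictability figure, so there is none to reproduce.

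**Inputs.** Block size 4, ratio 1:1 and four strata (Treatment allocation); N = 150 (Sample size). The stratum sizes, how much of the history the examiner knows, and whether the examiner sees the ODI category are not given. They are varied as assumptions below.

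**1. One block, full knowledge.** A 1:1 block of four has 6 equally likely sequences. An allocation is determined once one arm has used both its places.

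- Positions 1 and 2: never determined.
- Position 3: determined if the first two are alike, probability 2/6 = 1/3.
- Position 4: always determined.

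Expected determined allocations per block = 1/3 + 1 = 4/3, and (4/3)/4 = 33.3%.

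The best guess is right with probability 1/2, 2/3, 2/3 and 1 at the four positions. The mean is 2.833/4 = 70.8%, against 50% under simple randomisation.

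**2. Whole trial.** With complete blocks, 150/3 = 50 patients. Simulating 150 patients over four strata with incomplete last blocks gives about 48 (32%; 95% range 43 to 54). The result hardly changes for assumed stratum shares of 25/25/25/25, 10/10/30/50 or 5/5/40/50%.

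**3. Partial history.** Suppose each earlier allocation is known independently with probability q. Both members of the matching pair must be known, so the share is (q²/3 + q²)/4 = q²/3.

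| q | Share determined |
|---|---|
| 1 | 33% |
| 0.75 | 0.5625/3 = 19% |
| 0.50 | 0.25/3 = 8% |
| 0.25 | 0.0625/3 = 2% |

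Simulation agrees.

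**4. ODI category unseen, duration known, full history.** The allocation is certain only if the next place is determined in both candidate strata and points to the same arm: roughly 1/3 × 1/3 × 1/2 = 5.6%. Simulation with assumed shares of 10/10/30/50% gives 5.4%.

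**5. Other block schemes, full knowledge of history and stratum.** For the mixed schemes the observer is assumed to know the possible sizes but not their order.

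| Scheme | Share determined |
|---|---|
| Fixed 4 | 33.3% |
| Fixed 6 | 25.0% |
| Fixed 8 | 20.0% |
| Random 4/6 | about 5.5% |
| Random 4/6/8 | about 2 to 3% |

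Best-guess accuracy under 4/6/8 is about 68%.

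**The case against.** The strongest reply is that the allocation procedure is conventional and already protected. The list is computer-generated and held by someone outside patient selection. The examination is standardised, and a second research therapist is to attend, depending on availability. When two are present, classification is by consensus. Reasons for exclusion are registered, so selective exclusion would leave a trace. These safeguards lower the risk. They do not remove the predictability: the second examiner may be absent and, as a research therapist, is also described as not blindable. The consensus rule is stated for classification, not exclusion, and a register records exclusions without preventing them.

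It is also fair to say that best-guess accuracy falls only from about 71% to 68% under varying blocks. The gain lies mainly in removing certainty.

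A reader might infer more than the article supports in four ways:

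- **That a third of allocations are in fact predictable.** This needs the complete history and the scored ODI. The questionnaires are completed before the examination, but nothing says the examiner sees the score. Research therapists are kept out of outcome data collection, and it is unclear whether that covers baseline.
- **That all eligibility decisions are exposed.** At the telephone check the baseline ODI has not been collected, so the stratum is not yet fixed. The concern is with exclusions at the examination.
- **That the other research therapists finish before randomisation and so could obviously be blinded.** The usual-care section has them supplying a written medical history to the usual-care therapist, which may be a task after allocation that reveals the arm.
- **That publishing the block size causes the problem.** The article does not show that publication came before recruitment, and the investigators know the size anyway.

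**Conclusion.** The concern holds as a weakness in design, not as evidence that concealment failed or would be abused. A single block size of four, with an unblinded examiner who monitors the therapists, puts the determined share at no more than about one third (some 48 of 150 patients) at the final eligibility decision. That upper limit assumes knowledge of all earlier allocations in the stratum and of the current patient's stratum. Under weaker assumptions the share is 19%, 8% or 2% as the known history falls to 75%, 50% or 25%, and about 5% if the ODI category is not seen. The article does not settle which applies. The exposure is avoidable at little cost, so the change is worth making even if the true share is at the lower end.

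**What to change.** Generate the lists with block sizes varying at random within each stratum, for example 4, 6 and 8, with the sizes and their order known only to the independent researcher. Moving to a larger fixed block is not enough: a fixed size of 8 still leaves 20% determined. Varying sizes do not bring the figure to zero. If the possible sizes are known, four like allocations at the start of a stratum can come only from a block of 8, which settles the next four.

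Where feasible, let the independent researcher send the arm-specific documents to the treating therapists: the medical history for usual care and the classification result for the classification arm. Examining research therapists who do no monitoring then need not learn allocations, and the Blinding section can distinguish them from those who must. The principal investigator stays unblinded while monitoring, so the block-size change is the main remedy.

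The cost is a regenerated list and a changed hand-over of documents. The largest end-of-stratum difference between arms rises from 2 to 4, so the worst case over four strata rises from 4 × 2 = 8 to 4 × 4 = 16 patients.
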